## Abstract

**Background:**

People with severe mental illness (SMI) are less physically active and more sedentary than healthy controls, contributing to poorer physical health outcomes in this population. There is a need to understand the feasibility and acceptability, and explore the effective components, of health behaviour change interventions targeting physical activity and sedentary behaviour in this population in rural and semi-rural settings.

**Methods:**

This 13-week randomised controlled feasibility trial compares the Walking fOR Health (WORtH) multi-component behaviour change intervention, which includes education, goal-setting and self-monitoring, with a one-off education session. It aims to recruit 60 inactive adults with SMI via three community mental health teams in Ireland and Northern Ireland. Primary outcomes are related to feasibility and acceptability, including recruitment, retention and adherence rates, adverse events and qualitative feedback from participants and clinicians. Secondary outcome measures include self-reported and accelerometer-measured physical activity and sedentary behaviour, anthropometry measures, physical function and mental wellbeing. A mixed-methods process evaluation will be undertaken. This study protocol outlines changes to the study in response to the COVID-19 pandemic.

**Discussion:**

This study will address the challenges and implications of remote delivery of the WORtH intervention due to the COVID-19 pandemic and inform the design of a future definitive randomised controlled trial if it is shown to be feasible.

**Trial registration:**

The trial was registered on clinicaltrials.gov (NCT04134871) on 22 October 2019.

## Background

People with severe mental illness (SMI) experience a higher prevalence of preventable physical health conditions compared to the general population [1]. In particular, people with SMI, such as schizophrenia-spectrum disorders, bipolar disorder and major depressive disorder, have a risk of cardiovascular and metabolic diseases 1.4–2.0 times higher than the general population [2]. Longitudinal data indicates that people with SMI are more likely to have two or more comorbidities, with greater increases in the prevalence of comorbidities over time in people with SMI compared with the general population [1]. Alongside factors including genetic risk and the side effects of anti-psychotic medications, the high prevalence of cardiometabolic-related morbidity and mortality in SMI has been associated with modifiable lifestyle factors, including reduced physical activity and high levels of sedentary behaviour [3].

Systematic review evidence has shown that people with SMI are less physically active and spend more time in sedentary behaviour than healthy controls [4–9]. They complete less moderate to vigorous physical activity than controls [9], with up to 70% not meeting physical activity guidelines [4, 10]. They also spend 8–11 h per day sitting or lying down, which represents more time in sedentary behaviour than healthy controls [4, 5, 7–9]. Higher levels of sedentary behaviour in SMI have been associated with poorer metabolic outcomes [11], while increased physical activity improves cardiometabolic risk [12]. Interventions that support those who are inactive to replace sedentary time with small amounts of physical activity are likely to reduce the incidence and impact of cardiometabolic comorbidities in people with SMI [13–15].

Barriers to being active experienced in the general population, such as time constraints and physical health concerns, are compounded in people with SMI due to their mental health symptoms. People with SMI report physical barriers, such as tiredness, low energy and sedative effects of their medications; psychological barriers, such as stress, depression and amotivation; and social and environmental barriers, such as lack of support and social isolation [16–18]. Given these barriers, and the high levels of inactivity in people with SMI, walking has been recommended as one of the simplest ways of increasing physical activity [19]. Systematic review evidence shows small, short-term effects of walking on weight reduction (*n* = 10 trials, 339 participants) [20], and recent feasibility evidence by members of our team [21] showed that a walking-based intervention to increase physical activity and reduce sedentary behaviour in adults with SMI was feasible and acceptable, with positive findings in recruitment, retention, adherence and participant feedback and preliminary evidence for an increase in physical activity levels and reduction in sedentary behaviour in the intervention compared to the control group.

Although the study by Williams et al. [21] contributes to the developing knowledge base on walking interventions in people with SMI, it was conducted in a densely populated urban setting. Environmental design features of large cities, such as the walkability of streets, proximity of destinations and density of shops and services close to the home, strongly influence the likelihood of walking [22]. Conversely, residents of rural and semi-rural areas have to overcome additional unique barriers to engage in regular walking, such as a greater dispersion of housing, infrastructure and services leading to increased car-dependency and concerns about personal safety, for example walking on unlit rural roads without footpaths [23]. As such, an urban-based intervention may not be directly transferable.

This randomised controlled feasibility study aims to assess the feasibility and acceptability of a multi-component behaviour change intervention and explore its efficacy in improving physical activity and sedentary behaviours in adults with SMI living in rural and semi-rural environments. It also aims to explore effective intervention components to support health behaviour change in this study population. Findings will be used to optimise design of a main fully powered trial.

## Aims and objectives

### Aim

To test the feasibility of a multi-component behaviour change intervention aimed at increasing physical activity and reducing sedentary behaviour compared with a one-off education session in people with SMI living in rural and semi-rural locations.

### Objectives

i.To determine the recruitment, retention and adherence rates in both trial arms and explore reasons for these rates.ii.To determine the acceptability of the intervention in terms of the incidence of adverse events and level of overall satisfaction in both groups.iii.To estimate variability in clinical markers to inform the design of future effectiveness studies (calculate effect sizes for change in physical activity, sedentary behaviour and cardiometabolic risk factors, including BMI and waist circumference).iv.To conduct a process evaluation according to MRC guidance [24] to explore potential mediators of behaviour change (motivation to exercise and psychological needs satisfaction), to determine requirements for clinical staff to deliver the intervention, and service users views of the intervention.

## Methods

This section describes the planned methodology; changes made due to the COVID-19 pandemic are summarised later in Table 2.

### Study design

This feasibility study is a 13-week randomised controlled trial comparing the Walking fOR Health (WORtH) intervention, a group-based intervention including education, goal-setting, self-monitoring, and group walks, with a control consisting of a single education session during which participants receive written and verbal information on the benefits of being more active. A logic model detailing how the WORtH intervention may achieve its proposed outcome is presented in Fig. 1.

**Fig. 1 Fig1:**
[figure not shown]
A logic model of the proposed effect of the WORtH intervention on health in individuals with SMI

### Setting

The intervention will take place within the mental health service in two health care trusts in Northern Ireland (NI) and one in the Republic of Ireland (RoI).

### Approval

Ethical approval for the trial has been obtained from the Office for Research and Ethics Committees NI (IRAS ID: 250401) and the Health and Social Care Executive Dublin North East Research Ethics Committee in RoI. Local research governance approval was obtained from the relevant health care trusts. The trial has been registered on clinicaltrials.gov (NCT04134871).

### Study population

This trial aims to recruit 60 participants: 30 in the intervention group and 30 in the control group. A formal sample size calculation was not used for this feasibility study; it is anticipated that this sample size will provide sufficient information on the study objectives to inform a future main trial. The inclusion criteria will be adult participants (male or female; aged ≥ 18 years) with a diagnosis of any SMI (schizophrenia, psychosis, bipolar disorder and major depression), not meeting the national physical activity guidelines. A validated questionnaire, the General Practice Physical Activity Questionnaire (GPPAQ), will be used to screen physical activity levels [25]. Exclusion criteria will be those with significant movement impairment, those identified as ‘Active’ using the GPPAQ screening tool and those unable to understand English or who lack comprehension to understand the purpose of the study and give written informed consent. The revised Physical Activity Readiness Questionnaire (PAR-Q) [26] will be used to identify any health-related risks of exercising that would require a participant to consult their general practitioner prior to changing their physical activity levels.

### Recruitment

Recruitment to the trial will be via mental health teams in NI and ROI and will involve a number of strategies. The research team will work closely with the multidisciplinary mental health team clinicians and the Northern Ireland Clinical Research Network Mental Health group, where available, to identify service users who meet the eligibility criteria. Recruitment will be via screening clinic lists, referral from existing services, such as groups, day-care services and residential facilities, and through posters displayed in communal and waiting areas. Service users who meet the eligibility criteria will be given information about the study, either at a clinic visit or via post. Those who express an interest in taking part will be invited to meet with the researcher to complete the GPPAQ and PAR-Q and be given the opportunity to ask any questions they have about the study. Following this, if interested in participating in the study they will be asked to provide written consent.

### Randomisation

Cluster randomisation will be used given that some participants may be recruited from services such as groups, day centre or residential facilities. Each cluster will have a 1:1 probability of being allocated to intervention or control. The randomisation will be done by a researcher independent of the study and blind to the identity of the participants. A site will be ready for randomisation when all participants have consented and completed baseline assessment. Random allocation to intervention or control will be done when a group of sites are ready for randomisation.

### Intervention

Participants assigned to the WORtH intervention group will attend an initial educational group session where they will meet their clinician-coach, a clinician from the mental health team who has been trained to deliver the WORtH intervention. The content of the group education session will introduce the benefits of increasing their physical activity and reducing their sedentary behaviour, along with strategies to help them to move more and sit less in their daily routines. During the session, participants will be given a physical activity monitor (Mi Band 3, Xiaomi Corporation, Hong Kong) to self-monitor their daily steps throughout the intervention and an activity diary where they will record their physical activity and sedentary behaviour goals, complete their action plans and self-monitor by recording daily goal attainment.

Participants will be invited to attend a weekly group walk led by a clinician-coach; this will provide an element of social support. Additionally, they will meet with their assigned clinician-coach every 2 weeks. During coaching sessions, the participant will be supported to set move more (physical activity) and sit less (sedentary behaviour) goals which will be reviewed and progressed during the programme. Participants will be supported to complete an action plan of when, where and how they plan to meet their goals including strategies to overcome anticipated barriers discussed during the session.

The Behaviour Change Technique Taxonomy version 1 (BCTTv1) [27] provides a standardised and well-defined taxonomy of active components of behaviour change that can be used in the design and evaluation of interventions [28]. This approach has been used by our team to develop and define a number of physical activity and sedentary behaviour interventions [29–32] and helped to inform the behaviour change techniques (BCTs) to embed within the WORtH intervention to promote increased physical activity and reduced sedentary behaviour in people with SMI. WORtH intervention components were mapped to the BCTTv1 [27] independently by two authors ([name]) to identify the BCTs targeting increased physical activity and reduced sedentary behaviour in people with SMI. A summary of the core BCTs embedded within the WORtH intervention is presented in Fig. 2.

**Fig. 2 Fig2:**
[figure not shown]
Summary of behaviour change techniques included in the intervention

### Control

Participants assigned to the control group will be invited to attend a single one-to-one information session where they will be given an A5 leaflet briefly outlining the benefits of being more active and reducing sedentary behaviour and advice on how to do so. During the session, the researcher will read through the leaflet with the participant and give them the opportunity to ask questions. The researcher will complete a pro-forma with details of the duration of the session and a checklist of information to be covered in the session. At the end of the session, they will be informed of the date of end of study assessment. Immediately after the session, the researcher will make a handwritten note of the conversation and comments.

### Outcomes

#### Primary outcome

The feasibility and acceptability of the intervention will be evaluated in terms of recruitment, retention and adherence rates to the trial. Where available, reasons for these rates will be recorded (study objective I). A record will be kept of all information on instances of adverse events, including mental and physical problems and any reports of difficulty with intervention components (study objective II).

#### Secondary outcomes

The following outcomes will be measured at baseline and post-intervention, with a subset included at 6, 12, 18 and 24 months follow-up (study objective III) as summarised in Fig. 3:Objective sedentary and physical activity time: All participants will be asked to wear a wrist-worn triaxial accelerometer (Axivity AX3, Open Lab, Newcastle) for at least 4 days. The accelerometer will record how many minutes per day each participant is sedentary and engages in light, moderate and vigorous physical activities. This study will explore the change in average minutes of sedentary behaviour and physical activity before and after the intervention (study objective III).Anthropometric measures: Body mass index will be measured in line with the International Diabetes Federation criteria [33], including height, weight and waist circumference.Self-report of physical activity and sedentary behaviour: The Simple Physical Activity Questionnaire (SIMPAQ) will be used to capture self-reported physical activity [34]. The SIMPAQ includes five items asking about estimated time in bed, structured exercise participation and incidental or non-structured physical activity over the previous 7 days. The Sedentary Behaviour Questionnaire (SBQ) will be used to measure sedentary behaviour and has been shown to have good reliability [35].Mental well-being: Participants will be asked to complete the Warwick-Edinburgh Mental Wellbeing Scale (WEMWBS), a 14-item self-report measure, to assess well-being [36]. Respondents rate their experience regarding each statement over the last 2 weeks. Each item is scored using a 5-point Likert scale ranging from 1 (none of the time) to 5 (all of the time), with the total score ranging from 14 (low well-being) to 70.Functional mobility: Participants will be asked to complete a Timed Up-and-Go (TUG) test [37]. The TUG test requires participants to stand up from a chair, walk 3 m, turn around, walk back and sit down again. The time taken is measured in seconds, and scores represent functional mobility, with higher scores indicating increasing mobility difficulties. Times longer than 13.5 s are predictive of falls in the general older adult population.Motivation to engage in physical activity: Participants will be asked to complete the Behavioural Regulation in Exercise Questionnaire-2 (BREQ-2) which is a 19-item interviewer-administered questionnaire designed to consider an individual’s motivation towards exercise [38]. The BREQ-2 has been validated in people with schizophrenia [39]. They will also be asked to complete the Psychological Needs Satisfaction and Exercise Scale (PNSE), an 18-item questionnaire that measures perceived competence, autonomy and relatedness experienced in exercise contexts [40].

**Fig. 3 Fig3:**
[figure not shown]
SPIRIT schedule of enrolment, intervention and assessment

At baseline, socio-demographic information will be collected, including age, gender, ethnicity, living arrangements, pain level, smoking status, psychiatric diagnosis and current medications. Additionally, at baseline, all participants complete the Montreal Cognitive Assessment (MoCA) [41], a 30-item screening tool that is validated in SMI [42] and examines cognitive domains including executive functioning, attention and verbal fluency. Scores < 26 are suggestive of cognitive impairment. This data will be used to understand the implications of cognitive impairment on intervention delivery and completion of outcome assessments.

For the post-intervention assessment, attempts will be made to follow all participants, including those who discontinue the intervention early. Follow-up assessments at 6, 12, 18 and 24 months will be optional and will include the outcomes summarised in Fig. 3. Additionally, information on participants’ continuation with intervention components after the end of the programme will be collected.

Process evaluation (study objective IV): In addition to the outcome assessment, a qualitative process evaluation will be conducted to explore participants’ experience of the intervention, factors influencing engagement with the intervention and intervention changes required. Qualitative data from semi-structured interviews will be considered alongside the BREQ-2 and PNSE measures to consider how motivational constructs may mediate the effects of the intervention on behaviour change.

The process evaluation will also explore how the clinicians delivering the coaching intervention experienced this; qualitative data collection will explore their ability to deliver the instructions as planned, including facilitators and barriers to the delivery, the sufficiency of the training and the support from the research team. Members of the wider mental health care team who are involved in supporting participants with aspects of the intervention will also be invited to a focus group, dyad or interview (depending on the availability of individuals) to explore the level of support required by participants and the challenges and facilitators to complete the intervention from their perspective.

To explore the extent to which the intervention is delivered as planned, clinician-coaches will be asked to audio-record coaching sessions. Participants will be asked to consent to audio-recording of their coaching sessions. The audio-recordings will be reviewed alongside notes made in the study record forms by clinician-coaches documenting content of coaching session to assess delivery of the active components of the intervention against a study-specific pre-defined checklist based on the Borelli checklist [43, 44].

### Data analysis

Statistical analysis will be performed using SPSS software. The data will be checked for normality, then appropriate descriptive analyses will be used to summarise participant characteristics and outcomes. Feasibility, the primary outcome of this study, will be evaluated by calculating the percentage of people approached who participate in the intervention (recruitment) and the percentage who complete the intervention (retention and adherence).

As this is a feasibility study, significance tests will not be performed on secondary outcomes, such as change in anthropometric measures, physical activity or sedentary time. Intervention effects will be represented by point estimates and their standard deviations. Point estimates will be calculated by subtracting unadjusted mean data at each post-intervention timepoint from the mean data at the baseline timepoint. These will be used along with their standard deviations to estimate a sample size required for a definitive trial, if appropriate [45].

Qualitative data from interviews, dyads and focus groups will be transcribed verbatim, and interpretation, synthesis and data reduction will be undertaken independently by two members of the research team to identify relevant themes. Qualitative findings will be used alongside quantitative outcomes related to process evaluation (BREQ-2 and PNSE) to understand how the intervention was experienced by participants and any changes that they think would improve the intervention.

The traffic light system [46] will be used to guide progression to a main trial, as recommended in recent best practice, and will use the worst performing of the four elements in Table 1 to select which of the following actions to take:

**Table 1 Tab1:** Criteria for progression to main trial

	Red	Amber	Green

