**Signal of efficacy**			
**Results for primary clinical outcome and safety**	CI for effect estimate for primary clinical outcome that does not include a clinically important difference or evidence of significant harm	CI for effect estimate for primary outcome that is mostly negative or evidence of potential harm	CI for effect estimate for primary outcome that is mostly positive and no evidence of potential harm

**Green**: progress to main trial with a review of screening logs and protocol to address any barriers to recruitment, adherence or retention.

**Amber**: progress to main trial after discussion with Trial Steering Committee/Trial Management Group with a full review of screening logs and protocol deviations to implement solutions to barriers to recruitment, adherence or retention, and (if relevant) a review of feedback from participants and clinicians, and (if relevant) reconsideration of the intervention.

**Red**: probably not progress to main trial without substantial changes.

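### Effects are to be reported as differences of timepoint means with an undefined standard deviation, but the efficacy row of Table 1 is decided on a confidence interval

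*Protocol article*

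**What the plan says.** The Data analysis section of the protocol article sets out how effects will be shown: "Intervention effects will be represented by point estimates and their standard deviations". It then defines the estimate: "Point estimates will be calculated by subtracting unadjusted mean data at each post-intervention timepoint from the mean data at the baseline timepoint". That is baseline minus post-intervention, a difference between two timepoints. No difference between arms is described. The same section rules out testing ("significance tests will not be performed on secondary outcomes, such as change in anthropometric measures, physical activity or sedentary time") and gives the purpose of the estimates: "These will be used along with their standard deviations to estimate a sample size required for a definitive trial, if appropriate".

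Table 1, in the same section, governs progression. In its signal-of-efficacy row, green requires a "CI for effect estimate for primary outcome that is mostly positive and no evidence of potential harm" and red is a "CI for effect estimate for primary clinical outcome that does not include a clinically important difference or evidence of significant harm". Amber also turns on a confidence interval. The text above the table says that the action "will use the worst performing of the four elements in Table 1".

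Objective iii concerns variability for future studies, and its parenthesis reads "calculate effect sizes for change in physical activity, sedentary behaviour and cardiometabolic risk factors, including BMI and waist circumference".

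**The concern.** Two rules in the same section do not meet. One fixes how an effect is expressed: a difference of timepoint means with a standard deviation. The other fixes how an effect is judged: by where its confidence interval lies. An SD of individual values describes spread between people and does not shrink as the sample grows. A confidence interval describes the precision of the estimate and does shrink. Someone who followed the reporting rule alone would reach Table 1 without the quantity that its fourth row asks for, and that row can hold the trial at amber or red when the other three are green.

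A second, lesser difficulty lies in the word *their*. The standard deviations go into the definitive trial's sample size, but the text does not say whether they are SDs of each person's change or SDs of the values at each timepoint. These are different quantities, linked by the baseline to follow-up correlation, and the section does not mention that correlation.

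**Working it through.** The plan has no figure of its own to reproduce. The target of 60 (30 per arm, Study population) is stated without a formal calculation. The numbers below are illustrations on stated assumptions.

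**Inputs.** From the article: 30 and 30 participants; 1:1 cluster allocation before the COVID-19 suspension and 2:1 individual allocation after it; a red retention band below 65%. Assumed: SD at each timepoint = 1, correlation r between baseline and follow-up, effect of 0.5 SD, two-sided alpha 0.05, 80% power, clustering ignored.

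**1. What each rule yields.**

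| | Reporting rule (Data analysis text) | Decision rule (Table 1, row 4) |
|---|---|---|
| Contrast | baseline mean minus later mean | an intervention effect |
| Measure attached | standard deviation | confidence interval |
| Comparison of arms | not stated | needed for an effect of the intervention |

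**2. An SD does not show precision.** SD of change = √(2(1−r)). The 95% half-width for a between-arm difference in change is 1.96 × SD of change × √(1/n₁ + 1/n₂). At r = 0.5 the SD of change is 1.00 in every line below, yet the interval moves:

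- 30/30, all followed up: 1.96 × √(1/30 + 1/30) = 1.96 × 0.258 = ±0.51
- 30/30 at 65% retention (19.5 per arm): 1.96 × 0.320 = ±0.63
- 40/20, as if all 60 had been allocated 2:1: 1.96 × 0.274 = ±0.54

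Across other correlations at 30/30 with full follow-up, the half-width is ±0.60 (r = 0.3), ±0.39 (r = 0.7) and ±0.32 (r = 0.8).

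**3. Adding an interval to the stated estimate would not be enough.** For the within-arm change of 30 people at r = 0.5, the half-width is 1.96 × 1/√30 = 1.96 × 0.183 = ±0.36, against ±0.51 for the difference between arms. The within-arm interval is narrower and answers another question, because it contains any change that the control arm would also show. There is also a sign issue: with baseline minus post, a rise in activity comes out negative, while green asks for an interval that is mostly positive.

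**4. The meaning of SD changes the planned size.** n per arm = 2 × (1.960 + 0.842)² × (SD/0.5)², where (1.960 + 0.842)² = 7.85. With SD = 1 this is 2 × 7.85 / 0.25 = 62.8, so 63. With the SD of change, multiply by 2(1−r). With a baseline-adjusted analysis, multiply by 1−r².

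| r (assumed) | Timepoint SD | SD of change | Baseline-adjusted SD |
|---|---|---|---|
| 0.3 | 63 | 88 | 58 |
| 0.5 | 63 | 63 | 48 |
| 0.7 | 63 | 38 | 33 |
| 0.8 | 63 | 26 | 23 |

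The second and third columns agree only where 2(1−r) = 1, that is at r = 0.5. Which column is appropriate depends on the definitive trial's analysis. The feasibility report therefore needs to identify the SD and give r.

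**The case against.** The strongest reply has three parts.

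First, Table 1 sits within the Data analysis section and itself names the confidence interval, a ban on significance tests does not forbid one, and an interval can be computed from means, SDs and n. A condensed article may leave its level and formula to a fuller document. This stands as far as it goes: nothing prevents the interval from being calculated, and the missing level is no fault. What remains is that the article states a particular effect measure, and that measure is a timepoint difference with an SD. The between-arm interval follows from the summaries only if the SD is that of individual change and n is given. Timepoint SDs without the correlation do not yield it.

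Second, the ordinary reading of the SD may be the SD of change, since objective iii speaks of effect sizes for change. This also stands. On that reading the SD is suitable for a sample-size calculation based on change, so it cannot be said that the plan carries the wrong SD forward, only that it does not say which one. Nor is the SD of change the only usable input: a follow-up SD, with the correlation for a baseline-adjusted analysis, serves too.

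Third, large sample-size errors can be constructed but are not prescribed. A reader might take the SD of a difference of means literally as a standard error and infer a main trial 30 times too small (1/√30 = 0.183, variance ratio 30). A reader might also suppose that timepoint SDs would be combined as if independent, and infer a trial 2 to 5 times too large (1/(1−r) at r = 0.5 to 0.8). The arithmetic is right, but the article describes neither step, so these are not consequences of the plan.

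**Conclusion.** The point holds as a mismatch between the reporting rule and the progression rule, with an undefined SD as a secondary ambiguity. The mismatch needs no assumption: it can be read directly from the Data analysis text and Table 1, and it matters because the efficacy row alone can set amber or red.

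The sizes rest on assumptions. With unit SD, 30/30 analysed, clustering ignored and r between 0.3 and 0.8, the interval that Table 1 needs would be about ±0.60 to ±0.32 SD. For an effect of 0.5 SD at 80% power, the definitive trial would need 88 to 26 per arm with the SD of change, against 63 with the timepoint SD. The actual allocation mixes 1:1 clusters with 2:1 individuals, so neither 30/30 nor 40/20 is exact, and positive clustering would widen the intervals.

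A reader might also infer that the stated estimate is an arm-versus-arm difference of means. The text does not support that: it subtracts means at two timepoints, which takes it further from what Table 1 needs.

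**What to change.** Replace the two sentences that define how effects are represented and calculated with:

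> Intervention effects will be presented as the between-arm difference in change from baseline (or the baseline-adjusted difference) with its 95% confidence interval, without significance tests; this interval will be used for Table 1. Separately, for each outcome and arm, n, the SD at each timepoint, the SD of individual within-person change and the baseline to post-intervention correlation will be reported and used for the sample-size calculation.

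Choose one of the two contrasts, and state the direction of subtraction so that the favourable sign is clear for each outcome. The following sentence on sample size should then refer to these quantities.

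The change keeps the policy of no testing. The cost is analysis wording only, because every quantity comes from data already being collected, and the article reports the trial as still recruiting. The change does not by itself supply the primary clinical outcome or the clinically important difference that Table 1 also relies on. The article names neither, so the row should be checked against wherever they are defined.
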